### Trial design

2.1

This study is a multicenter, open-label, randomized, controlled, and equivalence trial with 2 parallel arms (1:1 ratio). The trial will be conducted at the Kyung Hee University Hospital at Gangdong (KHUHGD), Kyung Hee University Medical Center (KHUMC), Dongguk University Bundang Oriental Hospital (DUBOH), and Daegu Korean Medicine Hospital of Daegu Haany University (DKMHDHU). The efficacy and safety of Bosinji in patients with low back pain with radiculopathy due to LHIVD will be evaluated by comparison with loxoprofen, one of the NSAIDs.

This protocol has been approved by the Institutional Review Boards (IRBs) of the institutions (KHUHGD: KHNMCOH 2017-08-002, KHUMC: 170918-HR-039, DUBOH: 2017-0007, and DKMHDHU: DHUMC-D-17019). The trial has also been registered at clinicaltrials.gov, which is a website of the United States National Institutes of Health (registration number: NCT03386149), as well as in the Clinical Research Information Service of the Republic of Korea (registration number: KCT0002848). All research procedures comply with Korean Good Clinical Practice (KGCP) and the Declaration of Helsinki. The methodology was established in accordance with the Standard Protocol Items: Recommendation for Interventional Trials (SPIRIT)^[22]^ and with the revised Standards for Reporting Interventions in Clinical Trials of Acupuncture (STRICTA).^[23]^

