**Table 1 T1:**
[figure not shown]
Composition of Bosinji extract.

In the control group, Loxonin tablet (60 mg of loxoprofen, Dong Wha Pharm Co., Ltd, Seoul, Korea) will be orally administered 3 times a day at 30 minutes after each meal for 6 weeks. Three weeks of medication will be provided at week 0 and week 3, and the remaining medication will be withdrawn to confirm the medication compliance.

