### Sample size

2.8

The sample size was calculated based on a previous similar study (assuming σ = 9.18, 
[figure not shown]
 = 10),^[20]^ and the equivalence margin for the primary outcome was set at 18.^[34]^ With a 0.05 significance level, 80% power, and 1:1 ratio, we calculated the adequate sample size using the following formula:
 

Finally, we determined that the sample size required in each group should be 37 participants by considering the dropout rate (20%) and medication compliance rate (95%) on the calculated value. The 74 participants will be recruited separately at the four research sites; each site will recruit the following numbers of participants: KHUHGD: 20, KHUMC: 18, DUBOH: 18, and DKMHDHU: 18.

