### Statistical methods

2.11

The data will be corrected using the “last observation carried forward” method and then analyzed using the “intention-to-treat” principle. The independent *t* test and Chi-square test will be used to compare the differences in general characteristics between groups. As a primary outcome, changes in the 100-mm VAS for low back pain from baseline to the end of the end of the medication treatment will be compared between groups using an independent *t* test. Equivalence will be evaluated based on the equivalence margin of 18 mm and 95% confidence interval (CI). To compare the outcomes of each session with the baseline values, an analysis of covariance will be used. Trends over time and time-by-treatment interactions will be analyzed using a repeated measures analysis of variance. All statistical analyses will be performed using PASW statistics 18 for Windows, and the statistical significance level will be set at .05.

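### Equivalence is judged on the intention-to-treat set with LOCF and no other set is named, although the sample size allows for non-compliance and compliance data are collected

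*Protocol article*

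**What the plan says.** The Trial design section describes a randomised, open-label equivalence trial of two parallel arms. Under Sample size, the inputs are an SD ("assuming σ = 9.18"), a value of 10 taken from an earlier similar study, and a margin ("the equivalence margin for the primary outcome was set at 18"), in mm. The error rates and allocation follow: "With a 0.05 significance level, 80% power, and 1:1 ratio". The result is raised to 37 per group by "considering the dropout rate (20%) and medication compliance rate (95%) on the calculated value".

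Under Interventions, medication is dispensed at weeks 0 and 3, and "the remaining medication will be withdrawn to confirm the medication compliance".

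The Statistical methods section applies LOCF, after which the data are "then analyzed using the “intention-to-treat” principle". The primary comparison is an independent t test on the change in low back pain VAS to the end of medication. Equivalence is read from the 95% confidence interval against 18 mm. The article names no per-protocol or compliant set, and it gives the compliance data no role in the analysis.

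**The concern.** Two parts of the article point at different populations. The sample size makes an allowance for patients who do not comply, which makes most sense if they will be missing from some analysis. The analysis section keeps every randomised patient.

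In a superiority trial that choice is cautious, because dilution works against a positive result. In an equivalence trial it works the other way. Both arms receive the same weekly acupuncture, so patients who stay in the trial but do not take either drug are on the same background treatment. LOCF can add to this: a patient who leaves with only a baseline value is scored as zero change in either arm. If the drugs truly differ by the margin, each such patient pulls the observed difference below it. A positive result on this set alone would not separate two equivalent drugs from two drugs that were not fully taken.

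**Working it through.** **1. Reproducing the planned size.** Inputs from Sample size: SD 9.18, margin 18, value 10, 5% significance, 80% power. The formula and the symbol attached to the 10 are not legible in the text available. I read the 10 as the expected difference.

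n per arm = 2 x SD² x (z(0.975) + z(0.90))² / (margin - difference)²
= 2 x 9.18² x (1.960 + 1.282)² / (18 - 10)² = 27.67, so 28.

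Inflation: 28 / (0.80 x 0.95) = 28 / 0.76 = 36.84, so 37, the stated figure.

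The other standard variants, with the same inflation, miss it:

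| Variant | Before inflation | After inflation |
|---|---|---|
| One-sided 0.05, z(1-β/2) | 23 | 31 |
| One-sided 0.025, z(1-β) | 21 | 28 |
| One-sided 0.05, z(1-β) | 17 | 23 |
| Expected difference 0 | 4 to 6 | 6 to 8 |

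Inflating for dropout alone gives 28/0.80 = 35, so the compliance allowance supplies the last two patients per arm. Run in reverse, 37 x 0.80 x 0.95 = 28.1 compliant completers.

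**2. Effect of dilution on the stated rule.** Assumptions of mine: 37 per arm, SD 9.18, 95% CI rule, true on-drug difference exactly 18 mm. If a fraction f of one arm gets no differential drug effect, the expected difference is 18 x (1 - f), and that arm's variance rises by f(1 - f) x 18².

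Worked case, f = 0.05:
- Expected difference: 18 x 0.95 = 17.1.
- SE: √[(84.27 + 84.27 + 0.0475 x 324)/37] = 2.23.
- The upper limit falls below 18 with probability Φ[(18 - 1.96 x 2.23 - 17.1)/2.23] = Φ(-1.56) = 6.0%.

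The same approximation gives 2.5% at f = 0, 11.9% at f = 10% and 41% at f = 24%, where 24% is 1 - 0.80 x 0.95.

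Simulation (60,000 trials) with non-takers in both arms responding as to acupuncture alone, and Bosinji's effect over acupuncture set between 0 and 10 mm, gives:

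| Scenario (SD 9.18) | False equivalence |
|---|---|
| Full adherence | 2.5% |
| 5% non-takers (planned non-compliance) | 5-6% |
| 10% non-takers | 9-11% |
| 5% non-takers + 20% dropouts keeping 75% of drug effect | about 10-12% |
| Same, keeping 50% | about 17-21% |
| Same, keeping none | about 30-43% |

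**3. Sensitivity to the SD.** At SD 20, 5% non-takers give about 4%, and a full 24% with no drug effect gives about 13-14%. At SD 25 the 24% case gives about 11%.

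**4. Can the trial afford a per-protocol check?** At the planned difference of 10 mm and SD 9.18, the chance of meeting the rule is about 89% (t) to 90% (normal approximation) with 28 per arm, and about 96% with all 37. The planned power is 80%.

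**The case against.** The case on the other side has several parts, and much of it stands.

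- **Silence is not exclusion.** A reader might infer that compliant patients are never analysed and that no check exists. The article does not say so. It never restricts the analysis to intention-to-treat, it condenses a fuller protocol, and a statistical analysis plan that is not shown may name a further set. What remains is narrower: the article fixes the set and the rule for the equivalence decision, and that rule leans towards a positive result.
- **Intention-to-treat answers a legitimate question.** The Introduction calls for a pragmatic trial. With 24% untreated and an on-drug difference of 18 mm, the treatment-policy difference is 18 x 0.76 = 13.7 mm, inside the margin. Calling that result false presumes an on-drug question that the protocol does not state. This stands as a reason to keep intention-to-treat.
- **The compliance allowance does not itself define a per-protocol set.** It could be meant to offset dilution. This is fair. The figure 28 is reconstructed, not printed.
- **Dropouts are not non-takers.** A reader might infer a false-equivalence risk of 28-40% by treating the whole 24% allowance as patients with no drug effect. The documents do not support that as the expected case. Of the allowance, 20% is dropout and only 5% non-compliance. VAS is measured at week 3, so for anyone leaving after that visit LOCF carries an on-drug value forward.
- **A per-protocol set has its own selection bias,** which matters more in an open-label trial, and it is not guaranteed to be conservative. This stands too.

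**Conclusion.** The point holds in limited form and should be fixed. The stated decision rule uses intention-to-treat with LOCF and names no other set. The sample size is built around about 28 compliant completers per arm, and the compliance data have no stated use. That combination is anti-conservative for a claim of on-drug equivalence.

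At the planned 5% non-compliance the error rises from 2.5% to about 5-6%. With the planned dropouts as well it is about 10-21% if they keep 50-75% of the drug effect. The range of about 30-43% is a worst case in which every dropout keeps none.

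All these figures assume a true on-drug difference exactly at 18 mm, whereas the plan appears to expect 10 mm. They also assume SD 9.18, and they fall with a larger SD.

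A reader might go further and treat this as a defect that invalidates the primary claim unless both sets pass as co-primary tests on a covariate-adjusted interval. The documents do not support that: the primary comparison is a t test, the trial is described as pragmatic, and co-primary sets are only one accepted option.

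**What to change.** Before unblinding, pre-specify a per-protocol set: an observed week-6 VAS, compliance at or above a threshold chosen by the sponsor and measured from returned medication, and no major deviation. Repeat the same primary comparison in that set and read its 95% confidence interval against ±18 mm. State that the equivalence conclusion rests on consistency between the intention-to-treat and per-protocol results, with any disagreement reported and explained. The per-protocol set supplements intention-to-treat and does not replace it.

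The cost is a few lines of protocol or analysis-plan text and one repeated analysis on data already collected. The sample size need not change under the plan's own inputs. The 89-90% figure is for the per-protocol set taken by itself at the planned losses, so asking for consistency between the two sets slightly lowers the chance of a positive claim.

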##### 100-mm VAS for low back pain

2.6.1.1

The intensity of low back pain will be evaluated using the 100-mm VAS at pre-trial screening and at weeks 0 (baseline), 3, 6 (primary endpoint), and 10 (follow-up sessions).^[28]^ Participants will be asked to record their pain intensity within the past week on a 100-mm linear scale (0, absence of pain; 100, worst pain imaginable). Changes from baseline after 6 weeks of treatment will be compared between the groups as the primary outcome.

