### Randomization and allocation concealment

2.9

A total of 74 participants will be randomly allocated to the experimental group or control group according to a block randomization procedure with a 1:1 ratio after stratifying them by institutions. The randomization sequence will be generated by an independent statistician using the package “blockrand” 1.3 of R (The R Foundation for Statistical Computing, Vienna, Austria). For allocation concealment, sealed, opaque envelopes containing random code will be sent to each institution. The clinical research coordinator will open the envelope and allocate participants to their groups after screening.

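### The equivalence interval comes from an unadjusted t test on change; adding week-0 VAS and institution as covariates would be a free gain in precision, not the repair of an error

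*Protocol article*

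**What the plan says.** The primary outcome section states: "Changes from baseline after 6 weeks of treatment will be compared between the groups as the primary outcome". Under Statistical methods the quantity analysed is "changes in the 100-mm VAS for low back pain from baseline to the end of the end of the medication treatment". The test is named outright: this quantity "will be compared between groups using an independent *t* test". The decision rule follows directly: "Equivalence will be evaluated based on the equivalence margin of 18 mm and 95% confidence interval (CI"). No covariate is given for this comparison.

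The section on randomisation and allocation concealment specifies a "block randomization procedure with a 1:1 ratio after stratifying them by institutions". There are four institutions with fixed quotas ("KHUHGD: 20, KHUMC: 18, DUBOH: 18, and DKMHDHU: 18"). Low back pain VAS is recorded at week 0, so both candidate covariates will be available.

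Statistical methods also names an analysis of covariance for another purpose: "To compare the outcomes of each session with the baseline values, an analysis of covariance will be used". It is not linked to the equivalence decision.

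**The concern.** The trial's conclusion rests on where one interval lies relative to ±18 mm, so the precision of that interval matters. A t test on change subtracts baseline with a slope of exactly 1. If the true slope of week-6 VAS on baseline is lower, as regression to the mean would suggest, change stays correlated with baseline. Chance imbalance at week 0 then adds avoidable noise to the estimate. Randomisation balances the arms within institution, but the t test leaves variation between institutions in its error term, so the standard error is too large whenever institutions differ. What is at stake is interval width and power, in a trial of 37 per arm.

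**Working it through.** **Inputs.** From Sample size: SD 9.18; a value of 10 whose symbol is lost in a figure; margin 18; significance level 0.05; power 80%; dropout 20%; compliance 95%; 37 per arm. From Participants: entry VAS 40 to 80. Not in the article: the baseline-to-week-6 correlation ρ, the separate SDs at the two visits, the variance between sites, and whether 9.18 is the SD of change or of a single score.

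**1. The plan's own figure.** Take 10 as the assumed true difference and split both error rates between the two margins:

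n = 2 × 9.18² × (1.960 + 1.282)² / (18 − 10)² = 27.67, so 28 per arm; 28 / (0.80 × 0.95) = 36.8, so 37.

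The stated 37 reproduces, which supports reading 10 as the assumed difference.

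**2. Width under the planned test**, with 9.18 as the SD of change. Half-width = t × 9.18 × √(2/n).
- 37 per arm: 1.993 × 9.18 × √(2/37) = 4.25 mm.
- 28 per arm: 2.005 × 9.18 × √(2/28) = 4.92 mm.

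**3. Effect of a baseline covariate.** With s0 and s1 the SDs at baseline and week 6:
- Var(change) = s0² + s1² − 2ρ·s0·s1
- Var(ANCOVA) = s1²(1 − ρ²)
- Difference = (s0 − ρ·s1)², which is never negative.

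Apart from a few degrees of freedom, ANCOVA is therefore never less precise. With s0 = s1 the variance ratio is (1 + ρ)/2, and the width is multiplied by its square root:

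| assumed ρ | width factor | half-width, 37 per arm | half-width, 28 per arm |
|---|---|---|---|
| 0.3 | 0.806 | 3.43 mm | 3.97 mm |
| 0.5 | 0.866 | 3.68 mm | 4.26 mm |
| 0.7 | 0.922 | 3.92 mm | 4.53 mm |
| 0.9 | 0.975 | 4.15 mm | 4.79 mm |

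**4. When the gain disappears.** Entry is limited to 40–80 mm, while week-6 VAS is not, so s0 may well be smaller than s1. Two assumed cases, both with ρ = 0.5:
- s0 = 10, s1 = 15: variances 175 and 168.75, width factor 0.98.
- s0 = 10, s1 = 20: variances 300 and 300, slope 0.5 × 20/10 = 1, no gain.

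**5. Institution.** A simulation used the four site quotas split evenly by arm, a within-site SD of change of 9.18, equal SDs at the two visits, and 4,000 runs per setting. It compared the t test with a model on treatment, baseline and site. For site shares of variance from 0 to 10%, the width ratio ran from 0.81 to 0.78 at ρ = 0.3, from 0.87 to 0.84 at ρ = 0.5, and from 0.93 to 0.89 at ρ = 0.7. Coverage of the unadjusted interval was about 95% without a site effect and about 95.5 to 96% with one.

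**6. Power** (normal approximation, true difference 10). Unadjusted, it is about 0.96 at 37 per arm and 0.90 at 28. With baseline adjustment under equal SDs, the figure at 28 rises to 0.94 (ρ = 0.7) to 0.98 (ρ = 0.3).

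**7. The other reading of 9.18.** If it is a single-score SD, the SD of change is 9.18 × √(2(1 − ρ)). The unadjusted half-width at 37 per arm becomes 4.25 × √1.4 = 5.0, 4.25 and 4.25 × √0.6 = 3.3 mm at ρ = 0.3, 0.5 and 0.7. The width factors in step 3 do not change.

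**The case against.** The strongest defence is that nothing here is invalid. Under randomisation the t test on change is unbiased, and chance baseline imbalance is already part of its standard error. A wider interval makes a false claim of equivalence harder, not easier. The room between the assumed difference and the margin is 8 mm, against a half-width of 4.25 to 4.92 mm, so under the plan's own inputs adjustment saves under 1 mm. All of this stands, and it limits the weight of the point.

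Four stronger readings are tempting, and the article does not support them.
- A reader might infer that baseline is ignored. It is not: change from week 0 subtracts it. What is missing is an estimated slope.
- A reader might infer inflated type I error or an undermined sample size. Coverage is at or slightly above 95%, and 37 per arm reproduces with the unadjusted formula.
- A reader might take a 15 to 35% cut in variance as established. It needs equal SDs and a ρ of 0.7 to 0.3, neither of which is given, and the restricted entry range makes a smaller gain plausible. Carrying the last observation forward under intention to treat also points to about 37 per arm as the relevant number, not 28.
- A reader might infer two competing primary estimates at week 6. The ANCOVA sentence names neither a covariate nor a contrast between groups, and the t test is clearly designated primary. The link between the two is unclear, but there is no contradiction.

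The defence does not remove the point. The t test is a stated choice, not a detail left to an analysis plan, and a method that is at least as precise in expectation (a few degrees of freedom aside) is available from data already collected.

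**Conclusion.** The point holds as a free efficiency improvement, not as an error that must be fixed. Reading 9.18 as the SD of change, baseline adjustment would narrow the half-width at 37 per arm from 4.25 mm to between 3.43 and 3.92 mm, a saving of 0.3 to 0.8 mm. That range assumes equal SDs at the two visits and ρ between 0.3 and 0.7. The saving falls to about zero if the slope of week 6 on baseline is near 1. Institution adds a further gain only if sites differ, and the article gives no figure for that. Under the stated planning values the equivalence decision is unlikely to turn on the change.

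**What to change.** Make the primary analysis a linear model (ANCOVA) of week-6 low back pain VAS, or of its change, on treatment, week-0 VAS and institution. Judge equivalence by the adjusted treatment difference and its 95% confidence interval against ±18 mm. Keep the unadjusted t-test interval as a supportive result. State which comparison the ANCOVA already named under Statistical methods addresses, which covariates it contains, and how it relates to the primary comparison. Settle this before treatment codes are released to the statisticians, so that the choice of model cannot depend on the results.

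The cost is a sentence or two of text. No new data and no additional patients are needed, and the model uses four further degrees of freedom (one for baseline, three for institution).

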### Data collection and management

2.12

All research data will be collected and double-checked by two independent researchers based on source documents including the CRF. All sensitive information obtained from the trial will be confidentially preserved, and personally identifiable information will be discarded after a certain period, in accordance with the SOP. All researchers will be given training in protecting the privacy of participants.

### Quality control

2.13

To maintain the quality of the trial, the study procedure and documents will be periodically monitored by the Korean Medicine Clinical Trial Center.

## Discussion

3

Bosinji is a granule-shaped herbal medicine derived from *Ucha-Shinki-hwan,* which is described in a medical book called “*Je-Saeng-Bang*” written in the 13th century.^[6]^ Due to the characteristic of this herbal formulation composed of 10 kinds of herbs, *Ucha-Shinki-hwan* has been reported to have beneficial effects on various diseases including chemotherapy-induced neuropathy,^[35–37]^ diabetic neuropathy,^[38]^ and overactive bladder.^[39,40]^ In addition, its effect on low back pain with radiating pain was reported in an RCT; however, there were many unclear risks of bias in random sequence generation, allocation concealment, outcome assessment blinding, and incomplete outcome data. In addition, since the outcome measurement was only limited to pain, it is not enough to confirm the definite evidence due to the low quality of the report.^[20]^

To confirm the efficacy of Bosinji compared with NSAIDs for low back pain and radiculopathy caused by LHIVD, this RCT was designed in a methodologically rigorous, full-scale setting. The indicators for pain, function, QoL, and safety will be comprehensively evaluated, and DSKI will be assessed to reflect the diagnostic conception of traditional Korean medicine. Because *Ucha-Shinki-hwan* was originally designed to treat a group of complex symptoms called DSK,^[6]^ not a single specific symptom, it is necessary to verify the relation between the therapeutic effect and traditional diagnostic system.

Loxoprofen, used as an active control intervention in this study, is one of the NSAIDs in the propionic acid group.^[41]^ The clinical benefit of NSAIDs for LHIVD remains controversial; however, they are most commonly used for conservative treatment of LHIVD because inflammatory signaling plays an important role in the production of nerve pain.^[1,2]^ Therefore, NSAIDs have been used as a control intervention in studies attempting to identify a new therapeutic agent for LHIVD.^[42]^ Although patient blinding is not possible due to the differences in the shape of medications, bias can be minimized through blinding of assessors and statisticians.

As a concurrent treatment, acupuncture will be practiced to reflect the actual clinical situation in Korea. While about 90% of patients who visit Korean medical institutions due to low back pain choose acupuncture as a primary treatment, about 30% of patients opt for herbal medicine treatment.^[21]^ Therefore, evaluating the effects of herbal medicine along with acupuncture may help determine the practical usefulness.

The results of this study will suggest clinical evidence comparing Bosinji with NSAIDs by providing data about the changes in various measurements from the rigorously conducted trial. These findings will help clinicians to utilize Bosinji with acupuncture as a therapeutic option for patients with LHIVD.
